---

## 2 SUMMARY

### PROTOCOL IDENTITY AND AIM

|                 |                                                                                         |
|-----------------|-----------------------------------------------------------------------------------------|
| EudraCT-numBer: | 2010-018529-21                                                                          |
| Protocol titel: | Albumin kinetics in general inflammation                                                |
| Study aim:      | Explore how general inflammation affects syntesis rate and capillary leakage of albumin |

### INVESTIGATIONAL MEDICAL PRODUCT

|                         |                        |
|-------------------------|------------------------|
| Product:                | SERALB-125             |
| Pharmaceutical form:    | Solution for injection |
| Mode of administration: | Intravenous injection  |

### METHODOLOGY

|                            |                                                                                   |
|----------------------------|-----------------------------------------------------------------------------------|
| Study design:              | Open explorative study                                                            |
| Dose:                      | 0,1+0,3 MBq                                                                       |
| Primary research question: | Is albumin synthesis rate and capillary leakage affected by general inflammation? |
| Effect parameters:         | Synthesis rate and capillary leakage                                              |
| Safety parameters:         | Vital parameters                                                                  |

### INVESTIGATED POPULATION

|                 |                                                       |
|-----------------|-------------------------------------------------------|
| Study subjects: | Patients undergoing scheduled major abdominal surgery |
| Number:         | Maximum 16                                            |

### TIME PLAN

|                         |         |
|-------------------------|---------|
| First patient included: | Q2 2010 |
| Last patient included:  | Q4 2010 |
| Last patient finalized: | Q1 2011 |

### 3 ABBREVIATIONS

---

| Abbreviation       | Unit              | Explanation                             |
|--------------------|-------------------|-----------------------------------------|
|  d-Phe |                   | Deuterium labeled phenylalanine         |
| AF                 | per min           | Respiratory rate                        |
| APE                |                   | Atom percent excess                     |
| ASR                | mg/kg/day         | Absolute Synthesis Rate                 |
| BMI                | kg/m  | Body Mass Index                         |
| Bq                 |                   | Bequerelle, radiation dose              |
| CRF                |                   | Case report form                        |
| CRP                |                   | C-reactive protein                      |
| FSR                | %/day             | Fractional Synthesis Rate               |
| J alb   | mg/kg/hour        | Mass flow of albumin from plasma        |
| LPK                |                   | White blood cell count                  |
| MAP                | mmHg              | Mean Arterial Pressure                  |
| PV                 | liter             | Plasma volume                           |
| SIRS               |                   | Systemic Inflammatory Response Syndrome |
| TER                | %/hour            | Transcapillary Escape Rate              |

## 5 BACKGROUND

### 5.1 FLUID TREATMENT AND CHOICE OF THERAPY

Fluid therapy is important with regard to many different diseases. In anesthesia and intensive care an aggressive fluid therapy is a cornerstone in the treatment of sepsis, but is also very important during major surgery, with or without bleeding, and in connection with trauma. The choice of fluid in these situations have been discussed for decades, but consensus have not been reached. Firstly, there are different views on the amount of fluid to be given, and then whether colloids (infusions of albumin, dextran, starch, gelatin or plasma) are preferable to crystalloids (isotonic electrolyte solutions) or not. There are also strong controversies regarding the various colloids, and not least, about the benefits or risks of albumin. The literature is inconsistent in this regard, where albumin is highlighted as dangerous [Cochrane 1998], harmless [SAFE 2004, Cochrane 2004] or particularly valuable for certain ICU patients [Dubois 2006]. Some reasons for these different opinions are based on the unclear indication for albumin use, and the incomplete knowledge concerning the physiology and kinetics of albumin. This study is the first of a research program that focuses on clarifying some of these important points about the albumin physiology and kinetics. Ultimately, the aim is to design a larger study that provides answers to albumin role in anesthesia and intensive care, and thus the opportunity for an optimized fluid therapy for large groups of patients. There are no previous studies that measured leakage and rate of synthesis of albumin at the same time, much less repeated measures.

### 5.2 INFLAMMATION

General inflammation is strongly associated with sepsis, which is a condition with high mortality despite modern intensive care. In Sweden to conduct clinical trials in this patient group, however, suffers from problems concerning the written consent, as patients are often unable to provide one. A milder form of influence is systemic inflammatory response syndrome (SIRS), which is characterized by changes in body temperature, heart rate, respiratory rate and the amount of white blood cells in the blood (LPK). One difference between SIRS and sepsis is if there is an infection or not. Major surgery triggers a general inflammation, and it is well known that many of the phenomena observed in septic patients also occur after surgery or other trauma.

In general inflammation, albumin levels in blood plasma is often low, regardless of whether the condition is due to infection, trauma, surgery, or in critically ill patients in intensive care. Other proteins increase, however, so-called acute phase proteins. One explanation for the low plasma levels of albumin is that albumin molecules are escaping from the bloodstream through the capillary walls, capillary leak (TER), which can be measured with radioiodine labeled human serum albumin as the fraction of albumin in the blood that leaves the blood stream per unit time. In thoracic surgery has been shown that capillary leakage of albumin is increased by 100% within 7 hours after surgery [Fleck 1985]. In general acute inflammation associated with infectious disease such as pneumonia, elevated values of TER has been reported [Ballmer 94]. TER may also be affected by diabetes, hypertension, malignancy, liver cirrhosis and rapid intravenous infusion of crystalloids. As a model of sepsis or SIRS, volunteers have been given endotoxine intravenously. This triggers an influenza-like condition and some biochemical changes, but not enough that you should get a measurable change in albumin TER [van Eijk 2005].

### 5.3 ALBUMIN

Albumin is a medium size molecule, 69 kDa, and the predominant protein in plasma (40 g/l of total 70 g/liter). The half-life of albumin is 14-20 days, and it is synthesized in the liver. The synthesis occurs as a prealbumin whose tertiary structure is configured for export from the liver. The process from the start of synthesis to export takes approximately 30 minutes. Albumin has multiple physiological functions, represents 70% of the oncotic pressure of plasma and acts as a transport protein and endogenous scavenger. Lack of albumin can be acute or chronic. Acute shortage is associated with general edema, but in chronic deficiency (congenital analbuminemia) surprisingly moderate symptoms occurs [Koot 2004].

Albumin synthesis can be determined and quantified with great certainty [Ballmer 1990]. We have previously shown that ICU patients with multiple organ failure have greatly increased albumin synthesis [Essen 1998]. Furthermore, patients who undergo cholecystectomy during acute cholecystitis have higher albumin synthesis than those operated on in quiet phase [Barle 2006]. There is an older study in only 4 patients, which found decreased synthesis during inflammation, but with a different method of measurement [Moshage 1987]: This is partly supported by a number of animal studies that mainly used indirect methods [Vincent 2009]. However, there are reasons to believe that albumin synthesis is increased in many patients with generalized inflammatory reaction. The mechanisms and time course of this increase is unknown.

## **6 STUDY AIM**

The study aim is to identify changes in albumin kinetics in patients who develop a generalized inflammation after major abdominal surgery.

## **7 RESEARCH QUESTION**

### **7.1 PRIMARY QUESTION**

Are albumin synthesis rate and capillary leakage affected by generalized inflammation?

### **7.2 SECONDARY QUESTION**

Do changes in albumin kinetic variables (P alb, FSR, ASR, TER and Jalb) correlate to the degree of SIRS or the increase in CRP?

Do albumin kinetic parameters correlate with each other before or after surgery?

Does pre-operative body weight loss correlate with pre-operative albumin kinetic parameters?

## **8 ENDPOINTS**

### **8.1 PRIMARY ENDPOINTS**

Fractional synthesis rate (FSR) and absolute synthesis rate (ASR) for albumin. Transcapillary escape rate of albumin (TER) and mass flow from the blood (Jalb). P-albumin, plasma volume, body weight.

### **8.2 SECONDARY ENDPOINTS**

SIRS-criteria (body temperature, respiratory rate, heart rate, B-LPK) including CRP, before and after surgery.

Albumin kinetic parameters (P-albumin, FSR, ASR, TER, and Jalb).

Body weight and plasma volume, before and after surgery.

Pre-operative loss of body weight.

## 9 DESIGN

### 9.1 DESIGN OVERVIEW

The study is a prospective, open, explorative pilot study of surgical patients scheduled for major abdominal surgery, pancreatic resection. A low dose of radioactive iodine (SERALB-125), will be injected intravenously on two occasions to study the albumin kinetics. At the same occasion, a flooding dose of deuterium labeled phenylalanine will be given. The actual study time is estimated to be about four hours spread over two days. The kinetics will be monitored for 90 minutes after the injection has been given. The first dose will be injected on the day of surgery, the second about two days after surgery. All other treatment will be given according to routine clinical practice. Recruitment will continue until 10 evaluable patients have completed all measurements. The staff who perform the laboratory analyzes will be "blinded".

## 10 ASSESSMENTS AND PROCEDURES

### 10.1 DAY -14 (DAY -28 TO -2). PATIENT INFORMATION

The patients undergo the routine preoperative assessment by the anesthetist and have a meeting with the surgeon. Routine blood tests before surgery is taken and submitted to hospital laboratory. These include the P-creatinine. No study-specific samples are taken at this time. Patients are informed orally and in writing about the study and the study-specific procedures of the investigator or co-investigator. The patient receives written study information to take home to read. Consent may be obtained at this visit for those patients who are willing to give it. However, probably the majority of patients give their consent at admittance to the hospital the day before surgery.

### 10.2 DAY -1 (DAY -3 TILL -1) – CONSENT AND SCREENING

The investigator visits the ward where the patient is admitted. The investigator will answer any newly emerging issues and then obtain the written consent. Women of childbearing capacity will have a U-pregnancy test. The investigator verifies that the blood samples taken at the -14 day visit are answered, and that the patient meets all inclusion criteria and no exclusion criteria exist. Chemotherapy or antibiotic treatment should be documented in the CRF. All other care given in the ward before surgery is standardized and according to local procedures. The patient's height and weight are documented in the CRF, as well as weight loss of 6 months. Now, It will be noted in the patient medical record that the patient participates in a clinical trial in accordance with LVFS 2003: 6, Chapter 3, 4§.

### 10.3 DAY 0 – DAY OF SURGERY, RADIOIODINE FIRST DOSE

In the morning of the day of surgery, the patient arrives to the pre-anesthesia ward about two hours before anesthesia startup (this is the "overtime" in addition to clinical practice) and meets an investigator and a research nurse who is well informed about the study. The usual measures before this kind of major surgery is performed in accordance with local routines, including an artery line and an intravenous peripheral catheter. Blood pressure, pulse and respiratory rate followed. Temperature, pulse and respiratory rate are documented in the CRF. Blood samples for determination of P-albumin and P-CRP are collected for analysis at Studieceter at Karolinska University Laboratory, Solna. B-LPK is analyzed at the routine hospital laboratory. Then, the patient receives an injection of radioiodine labeled albumin (SERALB-125, 0.1 MBq). A flooding dose of isotope-labeled phenylalanine is supplied over 10 minutes. Blood samples (total 46 ml) are taken at 0, 5, 10, 15, 20, 30, 40, 45, 60, 70, 80 and 90 minutes after injection of radioiodine and the start of the flooding dose of isotope-labeled phenylalanine, for determining the enrichment of the isotope phenylalanine in the blood, for the measurement of capillary leakage of albumin, and for determination of plasma volume. Then, anesthesia, surgery and postoperative care are performed according to standard procedures at the Karolinska University Hospital Huddinge.

#### 10.4 DAY 2 (DAY 1 TO 4) – RADIODINE SECOND DOSE

The investigator is responsible for documentation of postoperative complications in the CRF. Any lack of evaluability is assessed and documented in the CRF (see paragraph 11.3). New P- albumin and P- CRP are received as described above, and respiratory rate, pulse and body temperature noted in the CRF. The same study procedure as "day 0 - day of operation" is implemented as a second series of measurements in the same way over 90 minutes with radioiodine labeled albumin and a flooding dose of phenylalanine, although at higher doses to compensate for the increased background from the first measurement (blood samples, a total of 41ml).

#### 10.5 DAY 5 (DAY 4 TO 7) – FOLLOW UP

At least three days after the second series of measurements the investigator notes any complications in the CRF. A copy of monitoring hospital records are taken and patient identity concealed. These are attached to the CRF.

### 11 METHODS AND HANDLING OF SAMPLES

#### 11.1 METHOD

Measurement of radioactivity will be performed by scintillation counting at the Department of Nuclear Medicine, Karolinska Huddinge. Quantitative measurement of enrichment of isotope-labeled phenylalanine will be performed using gas chromatography-mass spectrometry at the Karolinska Stable Isotope Core where [name] is laboratory manager. Quantification of total phenylalanine (precursor) will also occur with mass spectrometry compared to an internal standard.

#### 11.2 HANDLING OF SAMPLES

The plasma samples for the measurement of stable isotopes will get de-identified labels, and will be kept in the existing bio bank at the Department of Anesthesiology and Intensive Care, Karolinska University Hospital Huddinge at -80 °C pending completion of the data collection, and then analyzed in the same run to obtain the best possible accuracy in accordance with local standard operative procedures. Sample Collection Manager is [name]. All testing materials will be destroyed when the material is published. Passkey will be stored in a locked room at the Department of Anesthesiology, internal address B43. Responsible for this is [name].

#### 11.3 ANALYSIS

The step from fractional synthesis rate (FSR %/d) to absolute synteshanstighet (ASR mg/kg/d) is taken by multiplying FSR by the intravascular albumin mass (IAM, g), which in turn is a product of the P- albumin and plasma volume (PV) and finally dividing the result by the body weight. Similarly, the total mass flow rate of albumin from the blood (Jalb) is calculated from the transcapillary albumin leakage (TER).

## 11.4 FLOW CHART

[figure not shown]

## 12 SUBJECTS

### 12.1 INCLUSION CRITERIA

- Patients scheduled for major abdominal surgery, pancreatic resection
- Males and females ≥ 40 years
- Written informed consent

### 12.2 EXCLUSION CRITERIA

- Pregnancy or breast feeding patients
- Patients planned for perioperative albumin/plasma infusion (primarily in chronic renal dysfunction but perhaps also in some kinds of coagulopathy)
- P-creatinine > 110
- Allergy to the investigational medical product
- Other circumstance that causes the investigator to judge the patients participation as unsuitable.

## 13 CRITERIA FOR DISCONTINUATION

### 13.1 PATIENT CRITERIA

*The patient may, at any time during the study, chose to end his/hers further participation in the study, without giving any cause.* If possible, the investigator/nurse will record the reason for study end in the CRF.

### 13.2 INVESTIGATORS CRITERIA AND EVALUABILITY

The primary investigator can determine that the patient cannot stay in the study. This can be founded on lack of evaluability or the reasons stated below:

- Errors in technical equipment
- Staf shortage that makes safe and standardized methods impossible.
- Ongoing major bleeding
- Massiv transfusion of albumin or plasma

This shall be stated in the CRF with date and time.

### 13.3 SUBJECT LOG

The investigator will keep a record of all patients informed about the study on a log list. The log list is stored in the investigator brouschure available on Department of Anesthesiology. It will show included and not included subjects.

## 14 TREATMENT

### 14.1 INVESTIGATIONAL MEDICAL PRODUCT

SERALB-125. Solution for injection 1.7 ml. Contains 320 kBq  $^{125}\text{I}$ -HSA (human serum albumin, corresponding to 100  $\mu\text{Ci}$ ). The dose 0.1 and 0.3 MBq at the first and second occation, respectively, is given as an intravenous injection.

SERALB-125 is approved for this purpose in France. For more details see appendix 1 (SPC).

### 14.2 PACKING, LABELING AND HANDLING OF THE INVESTIGATIONAL MEDICAL PRODUCT

The investigational medical product is produced in France, and imported to Sweden by [name] at **Electra-Box AB**, [name]. Then the drug is transported to Karolinska University Hospital Huddinge, to hospital pharmacy, and finally to the Department of Nuclear Medicine. There radioactivity in plasma is assessed. The local routines for the documentation and delivery to medical wards of radioactive compounds will be applied. Disposal of surplus material and samples will be in accordance with local routines at Dept of Nuclear Medicine, Karolinska University Hospital, Huddinge.

### 14.3 DRUG COUNTING

The investigational medical product will be collected at the Department of Nuclear Medicine to each patient and the ampoule will be labeled in accordance with appendix 2.

Doses collected from Dept of Nuclear Medicine will be documented in special medicine log list that is available in the investigator binder. There, each patient's dose is documented with date and time.

## 15 ASSESSMENT OF SAFETY AND EFFICACY

The primary investigator has undergone radiation protection training (Appendix 3). A meeting with [name] (Radiation nurse Nuclear Medicine Karolinska Solna) and the employees to be included in the study team is planned before the start of the study, *i.e.* when the investigator receive MPA's approval. There everyone will be informed about the measures Radiation Protection Committee deems necessary for waste handling, labeling of test tubes, etc. Application to Radiation Protection Committee at Karolinska Huddinge and Ethical Review Board in Stockholm takes place in parallel with application to the MPA.

### 15.1 ASSESSMENT OF PATIENT SAFETY

Patients will be monitored in the surgical ward, pre-anesthesia ward and intermediate ward K44, respectively, for the time when SERALB-125 is injected by a staff that is familiar with emergency incidents. Monitoring of the patient's heart rate, ECG, respiratory rate, oxygen saturation (oximetry), blood pressure and temperature are taken before and during the first 90 min after injection.

### 15.2 ASSESSMENT OF ANALYSIS RESULTS

Laboratory samples taken before and after surgery (*i.e.* P-creatinine, P-CRP, B-LPK) will be analyzed at the ISO certified Karolinska University Laboratory, Huddinge. Blood gases are analyzed by analyzers at the Department of Anesthesiology. P-albumin will be analyzed by immunochemical method through the Studieceter at the Karolinska University Laboratory, Solna. Other samples are analyzed as described in paragraph 9.

## 16 MANAGEMENT OF ADVERSE EVENTS

### 16.1 DEFINITIONS

In such major surgical procedures that occur in this study, all patients will pre- or postoperative encounter what in other contexts would be classified as AEs/SAEs. The surgery itself causes hospitalization (SAE). Anticipated effects of anesthesia or surgery will not be reported, even if they can be considered undesirable. These do not relate to the isotope and are not under the control of the investigator. However, such medical events that may affect the study results or the evaluability will be listed in the CRF.

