#### 16.1.1 Adverse events (AE)

An adverse event is defined as a medical event that occurs from the time the patient receives the isotope injection to 90 minutes thereafter.

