#### 16.1.2 Adverse reactions (AR)

An adverse reaction is a harmful and unintended medical response to a medical product. For an AE to become an AR, the suspected association between the product and the reaction must at least be possible.

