### **16.2 ASSESSMENT OF ADVERSE EVENTS**

#### **16.2.1 Assessment of severity**

Each adverse event will be classified by the investigator as mild, moderate or severe.

**Mild:** The event does not affect the person's normal life.

**Moderate:** The event causes deterioration of function but does not affect health. The event gives discomfort and/or causes inconvenience.

**Severe:** The event causes deterioration of function or working capacity or endanger the health of the person.

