#### **16.2.2 Assessment of causality**

**Likely:** Clinical event, including abnormal laboratory analyzes, which occur within a reasonable time after administration of the intervention / study product. Unlikely that the event can be attributed to underlying disease, other drugs or other treatment.

**Possible:** Clinical event, including laboratory analyzes, which occur within a reasonable time after administration of the intervention / study product. The event might be explained by underlying disease or other drugs.

**Unlikely:** Clinical event, including abnormal laboratory analyzes, which can temporarily be related to the administration of the intervention / study product. The event is unlikely related to the intervention / study product and can be explained by other drugs or underlying disease.

**Not possible to classify:** The event cannot be classified because of missing information or that the event is not verified.

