## **17 REPORTING OF ADVERSE EVENTS**

### **17.1 REPORTING ADVERSE EVENTS (AE)**

All undesirable events that occur immediately adjacent to SERALB-125 dose should be considered as an AE and documented in accordance with ICH GCP principles.

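### The section 16.1 exemption for expected effects of surgery has no exception for the 90 minutes after injection, so it contradicts the AE rules in 16.1.1 and 17.1 and pre-empts causality grading

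*Protocol*

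**What the plan says.** Section 16.1 of the protocol opens the chapter on adverse events with an exemption: "Anticipated effects of anesthesia or surgery will not be reported, even if they can be considered undesirable". The reason given is a statement about the whole class: "These do not relate to the isotope and are not under the control of the investigator". One safeguard follows: "However, such medical events that may affect the study results or the evaluability will be listed in the CRF". The section lists no anticipated effects and sets no time limit on the exemption.

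The sections that follow state the general rules:

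- Section 16.1.1: "An adverse event is defined as a medical event that occurs from the time the patient receives the isotope injection to 90 minutes thereafter".
- Section 16.1.2: for an AE to become an adverse reaction, "the suspected association between the product and the reaction must at least be possible".
- Section 16.2.1: "Each adverse event will be classified by the investigator as mild, moderate or severe".
- Section 16.2.2 has four causality categories. The text for *Possible* includes: "The event might be explained by underlying disease or other drugs". *Unlikely* covers events that other drugs or underlying disease can explain.
- Section 17.1: "All undesirable events that occur immediately adjacent to SERALB-125 dose should be considered as an AE", with documentation to follow.

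On timing, section 10.3 places the first injection and its 90-minute series before anesthesia. Sections 9.1 and 10.4 place the second about two days after surgery (Day 1 to 4). The flow chart in 27.1 marks adverse events for collection on both Day 0 and Day 2.

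**The concern.** Sections 16.1 and 17.1 both turn on whether an event is undesirable. Section 16.1 leaves such events out if they are expected from surgery or anesthesia. Section 17.1 takes all of them in if they occur close to the dose. An event on Day 2 can meet both descriptions, and the protocol does not say which rule prevails.

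What is at stake is how well safety is ascertained. The summary names vital parameters as the safety parameters, and section 15.1 has heart rate, respiratory rate, oxygen saturation, blood pressure and temperature monitored during the 90 minutes. Section 5.2 describes the inflammation that follows major surgery by changes in temperature, heart rate and respiratory rate, among other signs. In the second window, a reaction to the tracer and an expected effect of surgery can therefore look alike. If 16.1 is followed as written, such an event may never be classified as an AE. It would then not be graded for causality, and it would not enter the adverse-reaction and SUSAR pathway of 16.1.2, 16.1.4 and 17.3.

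**Working it through.** The point rests on text and timing. The protocol gives no figure to reproduce, and the only arithmetic is a count of injections.

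**Step 1. Apply each rule to one event.** Take tachycardia or fever during the 90 minutes after the second injection, of a kind that could also be expected after pancreatic resection.

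| Section | Result for this event |
|---|---|
| 16.1 | Not reported; unrelated to the isotope by class |
| 16.1.1 | AE, because it falls in the window, whatever its cause |
| 17.1 | AE, because it is undesirable and close to the dose |
| 16.2.1 | As an AE, graded for severity |
| 16.2.2 | Open to *Possible* or *Unlikely* |
| 16.1.2 | Adverse reaction if the association is at least possible |

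Section 16.1 gives the opposite answer to 16.1.1 and 17.1. That is a contradiction in the wording. The conflict with 16.2.2 is of a different kind: that section only defines categories, but it provides for events with competing explanations, and 16.1 decides those explanations in advance.

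**Step 2. Find where the rules overlap.** In section 10.3 the patient arrives about two hours before anesthesia starts, the 90-minute series is completed, and anesthesia and surgery follow. The exemption has little to act on in that window. The second window lies wholly in the postoperative period, so the overlap falls mainly there.

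**Step 3. Count the affected injections.** Section 9.1 gives two injections per patient, of which the second is postoperative.

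- With the 10 evaluable patients at which recruitment is to stop (9.1, 18.3): 10 × 2 = 20 injections, of which 10 are postoperative.
- With the maximum of 16 patients (summary, 18.3): 16 × 2 = 32 injections, of which 16 are postoperative.

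The second count is a ceiling. It assumes that all 16 patients receive both injections, and a patient withdrawn under 13.2 may not receive the second.

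**Step 4. See what is recorded anyway.** Section 18.1 puts all vital-parameter values during and after injection on a record that belongs to the CRF, and keeps monitoring records until 3 days after the second series. Sections 10.4 and 10.5 have postoperative complications noted in the CRF. The raw signs are therefore kept. What 16.1 can remove is the classification of the event and the judgement on its cause.

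**The case against.** The best defense is that 16.1 is a preamble about the whole perioperative course. It explains why the ordinary effects of a major operation, and the hospital stay itself, are not treated as AEs or SAEs, and 16.1.1 and 17.1 then give the specific rule for the injection window. That is a sensible intention, and exempting expected surgical events is not an error in itself. But 16.1 does not state the limit, and its wording on undesirable events runs directly against 17.1. If the defense is right, the fix only writes the intention down.

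A reader might also infer stronger things, which the protocol does not support:

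- *That the second injection would be event-free by construction.* Only anticipated effects are exempt; other events in the window remain AEs. Section 18.2 also says that postoperative complications will be reported.
- *That a reaction would vanish from the record.* Step 4 shows otherwise. The limit of that safeguard is that recording a value is not the same as classifying an event, and the safeguard within 16.1 depends on study results or evaluability, which is not a safety criterion.
- *That 16.2.2 would force a grade of at least* Possible. It sets no minimum, and *Unlikely* is available.
- *That nobody would judge the cause.* Calling an event an effect of surgery is itself an attribution, and section 17.4 has a physician present or immediately available. What may be skipped is the formal grade.
- *That the risk is weighted to the second injection because it carries 0.3 of 0.4 MBq, or 75% of the activity.* That figure measures radioactivity. Nothing in the protocol ties an acute reaction of this kind to it.

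**Conclusion.** The contradiction stands. Section 16.1, read as written, exempts events that 16.1.1 and 17.1 make AEs, and it declares them unrelated before the grading that 16.2.2 provides. It can keep a possible tracer reaction out of AE classification, causality grading and adverse-reaction or SUSAR handling.

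The reach is limited: mainly the second injection, so 10 of 20 with 10 completers and at most 16 of 32, and only events that could pass as expected effects of surgery or anesthesia. The protocol gives no frequency for such events, so the number that would go unclassified cannot be estimated. The conclusion assumes that 16.1 applies inside the 90-minute window, which its text allows and nothing in the protocol rules out. The correction is worth making because it is small and removes a direct conflict in the safety rules.

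**What to change.** Reconcile 16.1, 16.1.1, 16.2.2 and 17.1 with two changes in 16.1:

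1. Limit the exemption to events outside the 90 minutes after each injection. State that every event inside that window is recorded as an AE under 16.1.1 and 17.1 and graded for severity and causality under 16.2, even if surgery or anesthesia could explain it.
2. For events in that window, replace the class-wide statement of no relation to the isotope with the grade under 16.2.2.

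The cost is about two sentences of protocol text and a few additional AE lines, most of them likely to be graded *Possible* or *Unlikely*, from at most 32 windows of 90 minutes. The vital parameters are already being recorded in those windows, so no new measurement is needed.
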